***Power***

The difference for the primary outcome variable between the intervention groups and the control group is based on a power of 0.90 and an alpha of 0.05. To detect an effect size of 0.6, each condition requires a minimum of 50 subjects. We have decided to use 80 subjects in each group to make up for those that we anticipate will be lost in the follow-ups.

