***Hypotheses***

Regarding the first aim, it is hypothesized that both the crisis plan facilitated through the patient’s advocate and by the clinician can reduce the number of psychiatric emergency visits and (involuntary) admissions as compared to the control group without a crisis plan. In addition, we expect a greater effect when the crisis plan is facilitated through the patient’s advocate as compared to the crisis plan developed with the clinician only. Furthermore, we expect greater effects on the patient’s satisfaction with treatment and psychological functioning when the crisis plan is facilitated through the patient’s advocate as compared to the crisis plan developed with the clinician only. Another aim of this study is to investigate the mediating mechanisms of the crisis plan. The expectation is that after creating the crisis plan, patients will show improvements in working alliance, insight into illness, self-efficacy, therapy adherence, acceptance of the illness and social support (see figure 1)**.**

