***Primary outcome measure***

Primary outcome measures are the number of the crisis contacts with the clinician or after-hours emergency services, the number of (involuntary) admissions and the length of stay in hospital. The data are collected from the patient administration system and the emergency services' electronic system.

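### The sample size and its alpha of 0.05 belong to one unnamed primary outcome, while the protocol lists three or four unranked primary outcomes and three group contrasts

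*Protocol*

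**What the plan says.** In the protocol's Power section: "The difference for the primary outcome variable between the intervention groups and the control group is based on a power of 0.90". Alpha is set at 0.05. It continues: "To detect an effect size of 0.6, each condition requires a minimum of 50 subjects". Recruitment is set higher, at 80 per group, "to make up for those that we anticipate will be lost in the follow-ups". The outcome is singular and not named, and only plan versus control is mentioned.

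In Primary outcome measure: "Primary outcome measures are the number of the crisis contacts with the clinician or after-hours emergency services, the number of (involuntary) admissions", followed by length of stay in hospital. The Abstract and the Design section also list several primary outcomes, and none is ranked first. The brackets around *involuntary* leave open whether all admissions and involuntary admissions are one outcome or two.

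In Hypotheses, each plan is expected to do better than control. The section then ranks the two plans, expecting more from PACP than from CCP: "In addition, we expect a greater effect when the crisis plan is facilitated through" (the sentence is cut here). That makes three contrasts: PACP v control, CCP v control and PACP v CCP.

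Statistical analyses names chi-square tests and an(c)ova for group differences. It does not say whether these are three-group or pairwise tests.

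**The concern.** The sections disagree on what the primary question is. A reader cannot tell which outcome the effect size of 0.6, the power of 0.90 and the alpha of 0.05 describe. An analysis plan written from this protocol would have to choose.

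The choice matters because nothing in the protocol stops a favourable result on any one listed outcome from being reported as a positive primary result at a nominal 0.05. The Discussion asks whether *either* plan type reduces service use, so success on one plan would also suffice. The alpha in the Power section would then not be the error rate of the trial's primary claim.

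**Working it through.** **1. The plan's own figure.** Inputs from the Power section: d = 0.6, power 0.90, alpha 0.05. Sidedness is not stated. For one outcome and one pairwise contrast, n per group = 2(z_alpha + z_power)²/d².

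- One-sided: 2 × (1.645 + 1.282)²/0.36 = 47.6, so 48 (49 with the t distribution). This is close to the stated 50.
- Two-sided: 2 × (1.960 + 1.282)²/0.36 = 58.4, so 59 (60 with the t distribution). This does not match.

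The 50 is therefore consistent with a single one-sided pairwise test on a single outcome. No allowance for several outcomes or contrasts is visible in it. The sidedness is a separate matter.

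**2. Number of primary comparisons.** There are 3 outcomes, or 4 if admissions are split, and 3 contrasts, or 2 if only control contrasts count. Three contrasts give 3 × 3 = 9 to 4 × 3 = 12 possible comparisons.

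**3. Family-wise error with no effect anywhere.** Simulation with 400,000 runs, three equal arms, contrasts sharing arms, normal outcomes with a common correlation r, and two-sided tests at 0.05. The protocol gives no correlation, so r is an assumption and is shown from 0 to 0.9. Each entry is the probability that at least one test is significant.

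| Outcomes | Testing | r = 0 | r = 0.5 | r = 0.8 | r = 0.9 |
|---|---|---|---|---|---|
| 3 | one three-group test per outcome | 14.3% | 12.7% | 10.1% | 8.5% |
| 3 | two control contrasts, ungated | 24.9% | 22.0% | 17.5% | 14.8% |
| 3 | three contrasts, ungated | 32.5% | 28.5% | 22.7% | 19.4% |
| 4 | one three-group test per outcome | 18.5% | 15.8% | 11.7% | 9.5% |
| 4 | two control contrasts, ungated | 31.7% | 26.9% | 19.9% | 16.5% |
| 4 | three contrasts, ungated | 40.7% | 34.4% | 25.6% | 21.5% |

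Checks by hand at r = 0: three three-group tests give 1 − 0.95³ = 14.3%. With a single outcome, three ungated contrasts give about 12.3%, so three outcomes give 1 − (1 − 0.123)³ ≈ 32.5%. Treating the nine tests as independent would give 1 − 0.95⁹ = 37.0%, which is too high because the contrasts share arms.

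With one outcome and pairwise contrasts tested only after a significant three-group test, the rate is 5.0%.

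**4. Power if several outcomes stay primary.** Two-sided t test for one pairwise contrast, d = 0.6, without the three-group gate:

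| Evaluable per arm | alpha 0.05 | 0.05/3 = 0.0167 | 0.05/4 = 0.0125 |
|---|---|---|---|
| 80 | 0.97 | 0.91 | 0.90 |
| 50 | 0.84 | 0.71 | 0.68 |

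**The case against.** **A multiplicity rule usually sits in the SAP, which is not shown.** This stands. The absence of such a rule is not the finding. The finding is that the Power section and the outcome section disagree on how many primary outcomes there are, and a SAP would inherit that disagreement.

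**The protocol does not say that nine to twelve tests will each be run at 0.05.** This also stands. A reader might infer that the trial has a false positive rate of 22 to 32%. The documents do not support that as a fixed property. The range needs three outcomes, ungated two-sided pairwise tests and a correlation between 0.8 and 0. The named chi-square and an(c)ova tests can be three-group tests, which lowers the rate to about 9 to 14%. On the other side, counting four outcomes raises it to about 41%.

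**Zero correlation is implausible.** Length of stay is zero without an admission, and involuntary admissions are a subset of all admissions. The lower part of each range is the more realistic one, but at r = 0.9 every multi-outcome row still exceeds 5%.

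**The comparison of the two plans may be subordinate, and length of stay is not in the Hypotheses.** Both are fair. The control contrasts alone still give about 15 to 25% with three outcomes. Two outcomes with one three-group test each give 1 − 0.95² = 9.8% at r = 0. Whether two distinct interventions against a shared control need joint error control is debated, but the surplus over 5% arises from the outcomes alone.

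**Only results favouring a plan would be claimed as success.** Counting only false positives in the hypothesised direction, three outcomes with three ungated contrasts still give 18.5% (r = 0) to 10.6% (r = 0.9).

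**Conclusion.** The point holds as an inconsistency inside the protocol. The Power section ties alpha, power and sample size to one unnamed outcome for plan versus control. Other sections fix three or four unranked primary outcomes and three contrasts. Which outcome the sample size and alpha belong to cannot be determined.

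The size of the consequence is conditional. If any primary outcome may carry the claim at 0.05, the family-wise error is above 5% in every multi-outcome scenario tried, from about 9% to about 41%. Where it falls depends on the number of outcomes, the assumed correlation (0 to 0.9) and whether pairwise contrasts are gated by a three-group test. No single figure in that range can be attributed to the protocol.

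**What to change.** **Preferred.** In Primary outcome measure, name one primary outcome and list the others as secondary. State whether all admissions and involuntary admissions are separate outcomes. In Power, refer to the named outcome. Test it with the three-group test at 0.05, and examine the three pairwise contrasts at 0.05 only if that test is significant. With exactly three groups this is a closed procedure: any two equal pairs imply that all three groups are equal, so no further adjustment is needed.

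**If several outcomes stay primary.** Run the three-group tests at Holm levels, with the first step at 0.05/3, or 0.05/4 if admissions are split. Test the pairwise contrasts within an outcome at the level at which that outcome passed, not at 0.05. Holm bounds the outcome-level claims. To bound the pairwise contrasts jointly even when some are null and others are not, keep every outcome at the first-step level.

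**Cost.** The change is one of wording. Under the preferred option, the demoted outcomes can no longer carry the primary claim. Under Holm with three outcomes, first-step power for d = 0.6 is 0.91 with 80 evaluable per arm but 0.71 with the protocol's own minimum of 50. Primary data come from administrative records, which may keep losses low, but the protocol recruits 80 precisely because it expects losses. This favours naming one primary outcome.

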***Statistical analyses***

Analysis will be performed according to the *intention-to-treat* principle. Group difference will be investigated by chi-square tests and an(c)ova.

A patient is an study completer when he or she has completed all three interviews. After the intention to treat analyses, we will also analyse the effects in those patients who have completed the crisis plan. The missing data of secondary and mediating variables will be replaced by the data of the last available measurement using the principle of *last observation carried forward*

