**Abstract**

**Background:** Crises and (involuntary) admissions have a strong impact on patients and their caregivers. In some countries, including the Netherlands, the number of crises and (involuntary) admissions have increased in the last years. There is also a lack of effective interventions to prevent their occurrence. Previous research has shown that a form of psychiatric advance statement - joint crisis plan - may prevent involuntary admissions, but another study showed no significant results for another form. The question remains which form of psychiatric advance statement may help to prevent crisis situations. This study examines the effects of two other psychiatric advance statements. The first is created by the patient with help from a patient’s advocate (Patient Advocate Crisis Plan: PACP) and the second with the help of a clinician only (Clinician facilitated Crisis Plan: CCP). We investigate whether patients with a PACP or CCP show fewer emergency visits and (involuntary) admissions as compared to patients without a psychiatric advance statement. Furthermore, this study seeks to identify possible mechanisms responsible for the effects of a PACP or a CCP.

**Methods/Design:** This study is a randomised controlled trial with two intervention groups and one control condition. Both interventions consist of a crisis plan, facilitated through the patient’s advocate or the clinician respectively.

Outpatients with psychotic or bipolar disorders, who experienced at least one psychiatric crisis during the previous two years, are randomly allocated to one of the three groups. Primary outcomes are the number of emergency (after hour) visits, (involuntary) admissions and the length of stay in hospital. Secondary outcomes include psychosocial functioning and treatment satisfaction. The possible mediator variables of the effects of the crisis plans are investigated by assessing the patient’s involvement in the creation of the crisis plan, working alliance, insight into illness, recovery style, social support, locus of control, service engagement and coping with crises situations. The interviews take place before randomisation, nine month later and finally eighteen months after randomisation.

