***Discussion***

The central research question in this study is whether either of the two crisis plan types can reduce the use of psychiatric emergency services, as well as the number and duration of (involuntary) admissions. The secondary research question is whether the intervention improves psycho-social functioning. The identification of the possible intervention mediating mechanisms offers a tool for use in the development of future preventive interventions. The comparison between the two crisis plan types provides insight into the question whether a crisis plan facilitated through the patient’s advocate is more effective than a crisis plan facilitated through the clinician only. The study has several limitations and strengths.

*Limitations*

Firstly, no structured diagnostic interview is used to confirm the DSM-IV diagnosis. We decided to use the clinical diagnosis as derived from the medical records because of the extensive nature of the interview, and because a structured diagnostic interview-derived DSM-IV diagnosis is of limited importance in the present study. The second limitation is the possible recruitment bias. Because of the ethical consideration the clinician is the first person who informs the patient of the study. Some clinicians may have preferences for some patients to participate in the study. There is some risk that it will not be possible to generalise the results based on the expected response of about forty percent of the participants [7, 8]. People who don’t want to participate may have experienced a compulsory admission in the past and feel demoralized and disempowered.

*Strengths*

Important strengths are the clinical relevance and design of this study. Although crisis plans are formally part of the treatment plans, in practice clinicians rarely use advance statements. The structure and supervision provided by this study will help participating clinicians to switch their working method into a more structured and preventive approach.

The participants are not screened for their ability to make a crisis plan and therefore represent a more general population of patients with psychotic and bipolar disorders than a selected group of patients. Besides that, the multisite character of this study may also increase the generalization of the results. Internal validity is protected by the structured protocol monitoring and supervision of the clinicians.

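### The primary outcomes are event counts and hospital days, but the named tests (chi-square, ANOVA/ANCOVA) ignore observation time and cost some power, and length of stay has no stated denominator

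*Protocol*

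**What the plan says.** The section Primary outcome measure gives three kinds of quantity. Two are counts: "Primary outcome measures are the number of the crisis contacts with the clinician or after-hours emergency services", followed by "the number of (involuntary) admissions and the length of stay in hospital". The third, the stay, is a number of days. The Discussion restates the research question with a different term: "as well as the number and duration of (involuntary) admissions". Figure 1 also speaks of number and duration. Neither term comes with a denominator.

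Statistical analyses names the methods in one sentence: "Group difference will be investigated by chi-square tests and an(c)ova". No test is assigned to an outcome, and no covariate, count model or observation time is mentioned. The population is stated: "Analysis will be performed according to the *intention-to-treat* principle".

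The missing-data rule leaves out the primary outcomes: "The missing data of secondary and mediating variables will be replaced by the data of the last available measurement". Those outcomes come from records: "The data are collected from the patient administration system and the emergency services' electronic system". The Power section raises the group size from 50 to 80 to allow for losses, and Ethical principles lets a patient stop at any time.

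**The concern.** The hypotheses are about how many emergency visits and admissions occur. Chi-square can only compare categories such as any against none, so it discards the number of events. ANOVA or ANCOVA on raw counts compares means that a few frequent users can dominate. Neither, as named, uses the time for which each patient was observed, so a patient whose records end early could be scored as having few events, which looks like a good outcome.

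The length-of-stay wording raises a separate question. Days in hospital per randomised patient can be compared under intention-to-treat. Duration of an admission exists only for patients who were admitted, and admission is what the plans are meant to prevent. If a plan prevented mainly short admissions, the remaining stays would look longer even while total days fell. A primary outcome whose direction may depend on the reading needs a definition.

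**Working it through.** **1. The planned figure.** The Power section gives 50 per condition for an effect size of 0.6, power 0.90 and alpha 0.05. Read as a comparison of two means, n = 2(z_alpha + z_beta)²/d²:
- one-sided: 2(1.645 + 1.282)²/0.36 = 47.6, so 48 (49 with the t distribution);
- two-sided: 2(1.960 + 1.282)²/0.36 = 58.4, so 59 (60 with the t distribution).

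The stated 50 is close to the one-sided result. Either way, the primary outcome was planned as a continuous mean.

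**2. Are many zeros likely?** The only event proportions in the protocol are those of the joint crisis plan study in the Background: 13% and 27% compulsorily admitted, so 87% and 73% were not. That supports many zeros for compulsory admission. It says nothing direct about crisis contacts or all admissions.

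**3. Unadjusted comparison, equal follow-up.** The protocol gives no mean or variance, so these inputs are assumed: negative binomial counts with variance m + k·m², control mean m, rate ratio 0.5, 80 per arm. The share of zeros is (1 + k·m)^(−1/k). The standardised difference is 0.5m divided by the root of the average of the two arm variances; for m = 1, k = 2 it is 0.5/√((3 + 1)/2) = 0.35.

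| m | k | zeros (control) | standardised difference | power, t test | power, negative binomial |
|---|---|---|---|---|---|
| 0.5 | 2 | 71% | 0.30 | 0.44 | 0.46 |
| 1.0 | 2 | 58% | 0.35 | 0.65 | 0.68 |
| 1.0 | 4 | 67% | 0.28 | 0.42 | 0.46 |

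At 50 per arm the ranges are 0.26 to 0.45 and 0.31 to 0.49. The gap is 2 to 5 points. With 400 replicates the simulation error of one power figure is up to √(0.25/400) = 0.025, so the consistent direction is more informative than any single gap. Type I error of the two-group and three-group tests was 0.040 to 0.054.

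**4. Both analyses adjusted for prior count.** The protocol allows ANCOVA, so the fair comparison is ANCOVA against a negative binomial likelihood-ratio test, each with the prior count (500 replicates, 80 per arm, rate ratio 0.5, assumed prior-count distribution; slope is how strongly history predicts outcome).

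| mean | dispersion | slope | ANCOVA | negative binomial | gap in points |
|---|---|---|---|---|---|
| 1.0 | 1 | 0.5 | 0.762 | 0.778 | 1.6 |
| 1.0 | 2 | 0.5 | 0.604 | 0.652 | 4.8 |
| 1.0 | 1 | 1.0 | 0.700 | 0.776 | 7.6 |
| 0.5 | 2 | 0.5 | 0.454 | 0.500 | 4.6 |

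Null rejection was 0.04 to 0.06 for ANCOVA and 0.04 to 0.07 for the likelihood-ratio test. Wald tests from a negative binomial model reached 0.08 to 0.09, which is why the test must be specified.

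**5. Unequal observation time.** Same true rate in both arms, mean 1 per full period, dispersion 2, 80 per arm, unadjusted comparison of counts:
- both arms fully observed: rejects 5.2%;
- one arm observed for 85% of the time: 8.3%;
- one arm observed for 70% of the time: 22.1%.

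For scale, going from 80 to 50 implies a loss of up to 1 − 50/80 = 37.5%. If all of it fell in one arm, halfway through on average, that arm's share would be 1 − 0.375 × 0.5 = 0.81. A share of 0.70 would need those patients to leave after a fifth of the period: 1 − 0.375 × 0.8 = 0.70. The last case is therefore extreme.

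**6. Length of stay.** Primary outcome measure plus intention-to-treat fits total days per randomised patient, with zeros. The Discussion and Figure 1 fit duration per admission. No sentence chooses between them.

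**The case against.** The other side has a good deal of force.

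- A reader might infer that the plan compares stays only among admitted patients. No section says so. The outcome section together with intention-to-treat reads naturally as days per randomised patient, and the duration wording sits in the Discussion and a figure. What stands is that the denominator is open.
- A reader might infer that follow-up is unequal by design. It is not: interviews end "nine month later and finally eighteen months after randomisation" for everyone. Primary data come from records, so a missed interview need not mean missing primary data. What stands is that losses and withdrawal are expected, and there is no rule for a patient whose records are incomplete. If observation time is shortened equally in all arms, the comparison loses power but is not biased.
- A reader might infer that the tests are invalid or give no usable effect measure. Neither is so. Type I error is near nominal with equal follow-up, and ANOVA or ANCOVA yields a mean difference with a confidence interval. Chi-square suits a yes/no admission outcome.
- Skew is assumed for most outcomes. Participants are selected for a recent crisis, and contacts with the clinician count, so zeros may be fewer there.
- Offsets and covariates are often left to a statistical analysis plan, which is not at hand. That is fair as to detail, but the protocol does name its methods, and they make no use of observation time.

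**Conclusion.** The point holds in a limited form. The named tests are serviceable but not the best choice for these outcomes. On assumed inputs a count model gains about 2 to 5 points of power unadjusted and 2 to 8 points with both analyses adjusted for prior count. A larger gain can be obtained by setting an unadjusted t test against an adjusted count model, but that is not a like-for-like comparison. On the same inputs, halving the rate is a standardised difference of 0.28 to 0.35, well below the planned 0.6, so the test is not the main limit on power.

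The stronger reasons to act are observation time and the definition of length of stay. Bias from the first depends on a difference between arms that the protocol neither predicts nor guards against. The second leaves open a reading that would break intention-to-treat, though the protocol does not adopt it. The change should be made before analysis; it does not call the design into question.

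**What to change.** 1. Analyse the number of crisis contacts and the number of admissions by negative binomial regression with log observation time as offset and with group, team (the randomisation stratum) and prior two-year count as terms. Use likelihood-ratio or robust tests, and report rate ratios with 95% confidence intervals. With 240 patients in eighteen teams (240/18, about 13 each), say how teams without events will be handled, for example by a random team effect.
2. State the record window, taken here as 18 months from randomisation, and when a patient's observation ends. The offset corrects for time observed, not for leaving that is related to crisis risk.
3. Define length of stay as total inpatient days over 18 months per randomised patient, zero if never admitted, compared by bootstrap or permutation. State the rule for records that end early. Use this one definition throughout.
4. Keep chi-square or logistic regression for any involuntary admission.

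The cost is wording and standard software; treatment and recruitment are unaffected, and the records are already the data source. The small downside is that a model-based rate ratio replaces a simple mean difference for the counts; the mean difference can still be shown descriptively.

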***Definition of the intervention***

The research intervention includes two forms of crisis plans. The first type of psychiatric advance statement is created by the patient with the help of a patient’s advocate (Patient Advocate Crisis Plan: PACP) and the second with the help of a clinician only (Clinician facilitated Crisis Plan: CCP). Both crisis plans describe how to recognize early signs of a crisis and how to provide adequate help. The plans are summarized on a small card the size of a credit card and folded into a plastic wallet that the user carries at all times. The card contains practical information to be used in times of crisis, for example who must be called, or what to do with pets.

The CCP is an advance agreement because the clinician and the patient formulate the content of the crisis plan together. The plan is based upon the principles of the ‘shared decision making model’ [12]. The PACP is a type of advance statement. In this case the clinician is less involved in the process of formulating the plan and therefore the PACP represents the “autonomy model” [12].

Naturally, crisis plans are constructed on a purely voluntary basis. It can only be formulated if both clinician and patient are willing to cooperate in this process (CCP), or when the patient desires to formulate it with his or her advocate (PACP). The plan is not legally binding, because a clinician may deviate from the content of the plan in times of crises if strictly necessary for the treatment of the patient.

*Chosen type of advance statement*

Henderson and colleagues have made a typology of advance statements [5]. Although advance statements in our study (PACP and CCP) show much similarity with advance statements described by Henderson [5], they differ from the described types in certain features. One important difference is the facilitation through a patient’s advocate. The patient’s advocate formulates the plan with input from the clinician. The two participating patient’s advocates in our study are experienced social workers. One of them is a consumer peer specialist. The CCP does not use a patient’s advocate to help make the plan. Both the PACP and CCP are disseminated in the mental health administration system.

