***Ethical principles***

The study protocol, information brochure and informed consent form were approved by the Dutch Union of Medical-Ethic Trail Committees for mental health organizations (registration number 7.109, CCMO-nr NL 16818.097.07)

The effects of a crisis plan are unknown at this moment and therefore we think it is justified to allocate the participants randomly over the three conditions.

The clinician informs the patient about the research. After permission is granted, the interviewer informs the patient of the research aims and randomisation method and asks for his or her written informed consent. The patient is free to refuse participation at any time during the research period, without having to disclose any reason why.

Participants allocated in the control group receive care according to standard practice, without the creation of a crisis plan. In case patients in the control group wish to create a crisis plan, this will be honoured at any time during the research period.

The collected patient data are treated according to the Medical Confidentiality Rules, and are kept in locked files cabinets. Access is limited to members of the research group and the medical ethical committee.

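### The added analysis of patients who completed a crisis plan is a non-randomised comparison; it should be labelled descriptive and backed by an estimate that keeps all randomised patients

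*Protocol*

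**What the plan says.** The Statistical analyses section of the Protocol sets the main principle: "Analysis will be performed according to the *intention-to-treat* principle". The methods it names are brief: "Group difference will be investigated by chi-square tests and an(c)ova". It then adds, after the intention-to-treat analyses, that "we will also analyse the effects in those patients who have completed the crisis plan". No comparator, adjustment, timing rule or interpretive limit is given for this added analysis.

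The set is not the same as the study completers defined in the same section: "A patient is an study completer when he or she has completed all three interviews". One set is about interviews, the other about the intervention.

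Other sections show how a patient enters the plan-completer set:

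- Definition of the intervention: "Naturally, crisis plans are constructed on a purely voluntary basis". On the clinician-facilitated plan it adds: "It can only be formulated if both clinician and patient are willing to cooperate in this process (CCP"). A PACP is made when the patient wants one.
- Intervention procedure: a PACP also involves negotiation with the clinician and is signed by the psychiatrist and the clinician. A CCP needs the signatures of everyone involved.
- Ethical principles, on controls: "Participants allocated in the control group receive care according to standard practice, without the creation of a crisis plan". And further: "In case patients in the control group wish to create a crisis plan, this will be honoured at any time during the research period".

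**The concern.** Randomisation makes the three arms comparable as allocated. It does not make the finishers in one arm comparable with everyone in another. Finishing a plan marks willingness, engagement and enough stability to get through several meetings and collect signatures. The Protocol's own model (Figure 1) links working alliance, insight, self-efficacy and adherence to fewer emergency visits and admissions. Patients who already have more of these are plausibly the ones who finish. The Limitations text points the same way when it suggests that people unwilling to take part may have a history of compulsory admission.

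Timing adds to this. Without a timing rule, a crisis that occurs while the plan is being made can stop it from being completed. The outcome then helps to decide who is in the set.

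Chi-square tests do not correct for such selection. Covariate adjustment in an ancova would do so only as far as measured baseline variables explain completion, and no covariates are named for that purpose. At stake is a supporting result that readers would naturally take as the effect of actually having a plan, and possibly as evidence on whether the PACP beats the CCP.

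**Working it through.** The Protocol gives no figure for this analysis, so there is none to reproduce. The check asks what the completer contrast shows when the plan has no effect at all.

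**Inputs**

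- Overall risk, the same in both arms under no effect: 27%. This is the control proportion compulsorily admitted in the earlier joint crisis plan trial cited in the Background.
- Patients per arm: 80 (Power).
- Share completing a plan, *c*: not in the Protocol. Assumed 60%, with 50% to 90% as a range.
- Risk among completers: not in the Protocol. Assumed 20% and 24%, with 27% and 30% shown for comparison.

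**Step 1. Risk in non-completers that keeps the arm at 27%**

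risk in non-completers = (0.27 − *c* × completer risk) / (1 − *c*)

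- Completer risk 20%: (0.27 − 0.6 × 0.20) / 0.4 = 0.15 / 0.4 = 37.5%.
- Completer risk 24%: (0.27 − 0.6 × 0.24) / 0.4 = 0.126 / 0.4 = 31.5%.

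**Step 2. What each analysis shows when the plan does nothing** (*c* = 60%, so 0.6 × 80 = 48 completers against 80 controls; pooled two-proportion test, two-sided 5%, normal approximation)

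| Completer risk | Non-completer risk | Apparent risk ratio, completers vs controls | False-positive rate |
|---|---|---|---|
| 20% | 37.5% | 0.20 / 0.27 = 0.74 | about 14% |
| 24% | 31.5% | 0.24 / 0.27 = 0.89 | about 6% |
| 27% | 27% | 1.00 | 5% |
| 30% | 22.5% | 0.30 / 0.27 = 1.11 | about 7% |

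The last row is a reminder that if patients with worse histories were the ones who finished, the sign would reverse.

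**Step 3. The same on a standardised scale**

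If would-be completers do better than the others by *D* standard deviations, completers differ from all controls by (1 − *c*) × *D* with no plan effect. For an assumed *D* = 0.5, with 80*c* against 80 patients:

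| *c* | Spurious benefit | False-positive rate |
|---|---|---|
| 50% | 0.5 × 0.5 = 0.25 SD | 25% |
| 70% | 0.3 × 0.5 = 0.15 SD | 14% |
| 90% | 0.1 × 0.5 = 0.05 SD | 6% |

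The problem shrinks as completion rises and vanishes at *D* = 0.

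**Step 4. Estimates that keep everyone, on the same numbers**

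In the first row of Step 2 the plan arm as randomised has risk 0.6 × 0.20 + 0.4 × 0.375 = 27%, and control has 27%, so the intention-to-treat difference is 0. The complier-average effect is that difference divided by the difference in the share with a plan: 0 / (0.6 − 0) = 0 if no control makes a plan. Neither is distorted by who chooses to finish.

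**Step 5. PACP completers against CCP completers**

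Both sides are selected after randomisation, by different routes: one with an advocate, one with the clinician only. Nothing makes the two selected groups alike in prognosis, so this contrast is non-randomised too. The Protocol gives no basis for saying which way it would be biased.

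**The case against.** The strongest reply is that this is a supplementary analysis. The intention-to-treat analysis comes first and carries the conclusion. That stands, and it limits the point to a supporting result. A reader might infer that the trial's main finding will be biased towards benefit; the Statistical analyses section does not support that.

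The comparator is also inferred. A reader might take it that the plan explicitly sets completers against all controls, but no comparator is written. It is only the natural reading for an effect of having a plan. The details may sit in an analysis plan that is not at hand. Even so, the Protocol commits to estimating effects in a set formed after randomisation, and the arm-to-arm contrasts that can be drawn from that set share the weakness.

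Controls are not wholly unselected. They were picked by clinician and researcher, agreed to contact and consented to possible allocation to a plan (Recruitment/procedure), with about forty percent expected to respond (Limitations). This narrows the willingness gap but does not close it. The Strengths text says that participants are not screened for ability to make a plan, and the flowchart has boxes for not receiving the intervention.

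Two further readings go too far. One is that PACP completion depends on the patient's wish alone: the Intervention procedure also requires negotiation with the clinician and signatures. The other is that the completer analysis disregards controls who make a plan: the text does not say how they are handled, and leaving them among controls would dilute any real effect rather than inflate it.

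Direction and size are assumptions. The Protocol reports neither completion nor completer prognosis. The illustration uses a binary outcome from another trial, whereas the primary outcomes here are numbers of contacts and admissions and length of stay.

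**Conclusion.** The point holds in a limited form. The completer analysis is non-randomised, against controls and between the two plans, and can mix a plan's effect with prognosis. The mechanism follows from the Protocol's own text. Bias towards benefit is plausible, not certain. Under no true effect, with 60% completion and a completer risk of 20% to 24% against 27% overall, the apparent risk ratio is 0.74 to 0.89; with equal prognosis it is 1.00. These figures rest on assumed completion and risks and show scale only. The intention-to-treat conclusion is untouched. The wording should be changed because, as it stands, the result can be reported as the effect of a plan without any caution.

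**What to change.** 1. In Statistical analyses, state that the analysis of plan completers is descriptive and non-randomised, name its comparator, and state that it supports no claim of efficacy and none that PACP is superior to CCP or the reverse.

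2. For the effect of having a plan, add a complier-average causal effect for each plan against control. It keeps all randomised patients, uses the randomised arm as instrument for a completed plan, and counts exposure from completions that are already tracked (Intervention procedure; Structured monitoring) together with any plan found in control records. Patients with an existing plan are excluded at entry, so a plan in a control record would be new.

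3. Present this as a sensitivity analysis and not as a replacement. It assumes that an unfinished plan has no effect. The Background says that the process of developing a statement may itself change coping and insight, and the Intervention procedure has prevention strategies discussed at the first PACP meeting, before a draft exists. Both make that assumption uncertain, and it should be stated with the result.

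**Cost.** A few sentences of text, a check of control records and a small extra analysis. Intervals will be wider: with 60% completing and no plans among controls, roughly 1 / 0.6 = 1.7 times as wide as the intention-to-treat interval, and wider still if controls make plans.
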